### Measures

Implementation outcomes will be based on principles and recommendations in the PRACTical planning for Implementation and Scale-up (PRACTIS) Guide,^20^ key outcomes of the RE-AIM framework (reach, effectiveness, adoption, implementation and maintenance)^30^ (see online supplemental file 3), and implementation determinants (eg, context, acceptability, adaptability, feasibility and dose).^31^ The PRACTIS Guide provides an iterative step-by-step process to prospectively plan for implementation and scale-up of interventions in community settings, with the aim to enhance the potential translatability and impact of interventions in real-world settings. Data will be collected via (a) *TransformUs Secondary* registration data; (b) website analytics (eg, the number of overall page views per school and the number of users visiting the resource pages); (c) the Australian government My School website https://www.myschool.edu.au/ (eg, school type), (d) a brief online survey completed by consenting teachers (at baseline and follow-up) via REDcap; (e) text messages sent regularly to teachers will be used to assess the frequency of intervention delivery via text messages up to three times per term and (f) a focus group with teachers asking about their experiences delivering the programme, including any barriers or enablers.

At the end of the 6-month intervention period, a subsample of consenting teachers will be invited to participate in a focus group approximately 1-hour long. We will conduct up to six focus groups in up to three states/territories (eg, up to two focus groups per state/territory). Each focus group will include up to 12 teachers, ideally from the same school (teachers from no more than two schools will be included in one focus group). To ensure timely participation, teachers will receive SMS/email reminders prompting them to complete the survey and respond to the text messages. Online supplemental file 3 provides a description of the different quantitative and qualitative methods used to assess four of the RE-AIM dimensions (effectiveness outcomes will be assessed in the effectiveness trial only). Online supplemental file 4 provides a detailed description of the different methods used to assess implementation and effectiveness trial outcomes (ie, data source, relevant trial/s, targeted participants, time points and context), which are briefly described below.

### Teacher-level outcomes

#### Self-reported sociodemographic characteristics, physical activity and perceptions of school readiness, climate and environment

During the TransformUs website registration process, teachers will be asked to report their age range, gender and years of experience working in the education sector (online supplemental file 4A). All consenting teachers to the research component will be provided with a link to an online survey (REDcap) and will be asked to report, current teaching role (eg, year level/s, subjects), and reason for deciding to participate. In addition, teachers will *self-report their usual physical activity* level in the past week (ie, adherence to the Australian physical activity guidelines)^32^ (online supplemental file 4D). *School readiness*, *school climate*, *school* environment and policies and *current practice* will be assessed via the teacher survey. These items were adapted from the *TransformUs* primary school implementation trial^23^ and consist of 5-point Likert scales ranging from 1 (strongly disagree) to 5 (strongly agree): *teachers’ perceptions about school readiness* (eg, ‘People who work in this school are committed to implementation of *TransformUs Secondary’*); *school climate* (eg, ‘In my school teachers will be expected to use *TransformUs* strategies and will be supported to integrate *TransformUs* into existing teaching and/or school practices and policies’); *school environment/policies* (eg, ‘Physical activity is a top priority at our school’, ‘Our school has policies that promote physical activity’) and *current practice* (eg, ‘Currently my school has organised physical activities at lunch/recess that students are interested in’). In addition, *teachers’ level of competence* for certain aspects of active pedagogy (lesson planning, managing the class, managing curriculum demands) will be assessed (eg, ‘For each aspect of active teaching and movement integration, indicate how you perceive your level of competence’) using a 5-point Likert scale ranging from 1 (very incompetent) to 5 (very competent). *Teachers’ barriers* to implementation of active breaks and lessons in their classes (eg, insufficient training, lack of time) will be assessed on a 5-point Likert scale ranging from 1 (no barrier or does not inhibit) to 5 (a major barrier)/strongly inhibits) (online supplemental file 4D).

#### Intervention implementation

Teachers will report via online survey at the end of the intervention period, the frequency, duration and level of confidence for incorporating each of the components of the *TransformUs Secondary* intervention (table 1). Their commitment to continue to deliver these strategies in the future will also be assessed. Strategies that helped teachers implement *TransformUs Secondary* (eg, participating in the professional learning session, having a *TransformUs* champion, actively involving students) will be assessed based on 12 questions adapted from the TransformUs Primary survey and School Implementation Strategies, Translating ERIC Resources (SISTER) implementation strategies^33^ (online supplemental file 4D). In addition to the implementation survey, teachers’ frequency of intervention delivery will be assessed three times per term throughout the 6-month intervention period using text messages during and after school hours at different times. Teachers will receive regular messages on their mobile phones asking them to nominate by a corresponding number which of the strategies they implemented that week (eg, Which of the following TransformUs strategies have you implemented in the last week?) (online supplemental file 4H).

#### Teachers’ perceptions of the program reach, effectiveness, adoption, implementation and maintenance

*Teachers' perceptions of the programme reach, effectiveness, adoption, implementation and maintenance will be assessed via the teacher focus groups*. The qualitative questions have been framed around the implementation outcomes framework proposed by Proctor *et al* (2011)^34^ (online supplemental 4I).

### Data analysis

All statistical analyses will be performed using STATA 18 for Windows (StataCorp LP). Descriptive statistics will be used to summarise quantitative data collected from surveys (eg, teachers’ self-reported sociodemographic information, physical activity levels, perceptions of school readiness, climate and environment, as well as teacher practices, competence levels and perceived implementation barriers). The survey data regarding programme Reach, Adoption, Implementation and Maintenance will be also presented descriptively.

Similar descriptive statistics will be used to summarise the data for intervention implementation, including frequency, duration and confidence levels for incorporating active lessons, breaks and homework, as well as a commitment to continue implementing these strategies. Additionally, analyses will be conducted to examine associations between implementation strategies and outcomes, using regression analysis.

Linear or logistic regression models will be used to examine associations between various factors (such as teachers’ sociodemographic characteristics, physical activity levels, perceptions of school climate, etc) and implementation level, adjusting for multiple comparisons. The implementation levels will be determined using methods from a prior evaluation of the *TransformUs* efficacy trial.^35^ In brief, teachers will be categorised based on the extent of implementation, determined by the proportion of the entire intervention delivered, considering both dose-delivered and fidelity. The implementation levels will be classified as: (1) ‘low’ (<33% of the entire intervention delivered); (2) ‘moderate’ (33%–67% delivered) and (3) ‘high’ (>67% delivered).

Qualitative data will be transcribed and thematically analysed using NVivo V.14. The coding and theme development process will initially follow a deductive approach, guided by the study aims and domains within Proctor’s implementation outcomes framework.^34^ Subsequently, an inductive method will be employed, driven by the content of the data itself. Two independent researchers will be responsible for coding the data.

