**Methods and analysis:**

A type II hybrid implementation-effectiveness trial will be conducted using a mixed-methods design. For the implementation trial, *TransformUs Secondary* will be disseminated via key organisations nationally (eg, state departments of education) and available to all Australian secondary schools (n=1453). Implementation outcomes will be evaluated using the RE-AIM framework (reach, adoption, implementation and maintenance). Data will be collected at the school and teacher levels via the TransformUs website (website analytics), descriptive quantitative surveys, text messages to teachers and qualitative interviews with teachers, students and representatives from key organisations. Descriptive statistics will summarise quantitative data, with regression analyses examining the associations between implementation strategies and outcomes. Implementation levels will be classified as low, moderate or high based on the extent of intervention delivery. Qualitative data will be thematically analysed.

We will assess effectiveness outcomes in 10 Victorian secondary schools using a pragmatic 1:1 waitlist control design. The target sample is 600 Year 7–10 students (12–16 years). Primary outcomes include adolescents’ physical activity and sedentary time (assessed with accelerometry), and secondary outcomes include health (sleep and well-being), class and school engagement (on-task behaviour assessed via classroom observation and school attendance) and sitting time (assessed with posture monitors). Descriptive analyses will summarise students’ demographics, physical activity, sedentary behaviour and engagement, while mixed models will evaluate intervention effects on these outcomes, adjusted for confounders. Additionally, qualitative data will be thematically analysed using deductive and inductive coding in NVivo.

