### Sample size and power calculation

In 2023, there were 1453 secondary schools (Government and Independent schools) across Australia.^29^
*TransformUs* Primary (2018–23), reached 25% of primary schools over 4 years^23^; however, because of the shorter timeframe for this trial, we are expecting that no more than 5% of eligible schools will register for the programme via the *TransformUs Secondary* website, which equates to approximately ~70 schools. Based on response rates from the *TransformUs* Primary trial, we expect that no more than 40% of school staff will consent to take part in the research component. Making the intervention available to all schools enhances the generalisation of results by reaching diverse student populations, ensuring consistent implementation, and testing in varied real-world contexts (across school types and states and territories). This approach increases the sample size, allows for replication of outcomes and provides valuable feedback for continuous improvement.

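### Implementation level is defined only as a three-level ordered category, but no stated form of linear or logistic regression is matched to it, and the underlying proportion delivered would be the better outcome

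*Protocol article*

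**What the plan says.** The Data analysis section of the implementation trial plans that "Linear or logistic regression models will be used to examine associations between various factors" (teachers' characteristics, activity levels, perceived school climate and so on) "and implementation level, adjusting for multiple comparisons".

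The same paragraph says how the level is obtained. Teachers are sorted by extent of implementation, "determined by the proportion of the entire intervention delivered, considering both dose-delivered and fidelity". The groups are "1) ‘low’ (<33% of the entire intervention delivered"), "2) ‘moderate’ (33%–67% delivered) and (3) ‘high’ (>67% delivered"). The method is taken from an earlier evaluation of the programme's efficacy trial, which is cited but not reproduced. The abstract repeats the grouping: "Implementation levels will be classified as low, moderate or high based on the extent of intervention delivery".

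On the size of the data set, the implementation trial's Sample size and power calculation section expects about 70 schools to register and "no more than 40% of school staff will consent to take part in the research component". It gives no number of teachers, and no power, alpha or effect size for this regression.

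**The concern.** The outcome named for the association models is implementation level, and the only definition of that term is an ordered category with three values. Two model families are offered, with no rule for choosing between them. Ordinary linear regression on the category needs scores such as 1, 2, 3, and so treats the step from low to moderate as equal to the step from moderate to high. Binary logistic regression needs two of the three levels to be merged, and the text does not say which. Leaving both choices open until the data are in hand also adds room for analytic flexibility.

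The proportion delivered must be calculated before it can be cut at 33% and 67%, so a finer outcome exists at no extra cost. Information matters here. The data come from volunteers in about 70 schools, consent is capped at 40% of staff, and the tests will be adjusted for multiple comparisons. What is at stake is the chance of identifying which teacher and school factors go with better implementation, a central question for the implementation arm of a hybrid design.

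**Working it through.** The article states no figure for this analysis, so there is none to reproduce. The check is a reading of the text, followed by an illustration of the loss.

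**Reading.** Set the elements of the Data analysis paragraph side by side:

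- Outcome of the models: implementation level.
- Definition of implementation level: low, moderate or high, and no other.
- Source of the level: proportion of the intervention delivered.
- Models: linear or logistic, with no link to a form of the outcome. Ordinal, multinomial and binary logistic are not distinguished.
- Clustering: no allowance for teachers within schools is named in this section. The effectiveness trial's Data analysis section does name random intercepts for its student models.

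**Illustration 1: the article's cut points, assumed distributions of the proportion delivered.** For a weak linear association, the share of information kept is the squared correlation between the coded level and the proportion, cov² / (var × var).

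Worked case, proportion x uniform on 0 to 1, levels coded −1, 0, 1 (the same as 1, 2, 3 for a correlation):

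- var(x) = 1/12 = 0.0833
- var(level) = 0.33 + 0.33 = 0.66
- cov = (1 − 0.67²)/2 − 0.33²/2 = 0.2756 − 0.0545 = 0.2211
- share kept = 0.2211² / (0.0833 × 0.66) = 0.89

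For high against the rest under the same distribution: cov = 0.2756 − 0.5 × 0.33 = 0.1106, indicator variance = 0.33 × 0.67 = 0.2211, share kept = 0.1106² / (0.0833 × 0.2211) = 0.66.

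The same calculation for other assumed shapes:

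| Assumed distribution | Low / moderate / high | Three-level score | High v rest | Low v rest |
|---|---|---|---|---|
| Uniform | 33 / 34 / 33% | 0.89 | 0.66 | 0.66 |
| Beta(2,2) | 25 / 49 / 25% | 0.84 | 0.57 | 0.57 |
| Beta(2,4), mostly low | 53 / 42 / 4% | 0.77 | 0.24 | 0.68 |
| Beta(4,2), mostly high | 4 / 42 / 53% | 0.77 | 0.68 | 0.24 |
| Beta(5,5), mostly middle | 14 / 72 / 14% | 0.70 | 0.41 | 0.41 |

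The three-level score loses 11% to 30%. A collapse to two loses 32% to 76%.

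**Illustration 2: a normal measure cut into ordered groups.** The information kept about a location shift is the sum over groups of (difference in normal density at the two boundaries)² / group probability. This is the most that an analysis of the ordered groups can keep.

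- Three equal groups: density at each cut 0.3636, so 2 × 0.3636² / (1/3) = 0.793.
- Assumed 70/25/5 split: densities 0.3477 and 0.1031, so 0.3477²/0.70 + (0.3477 − 0.1031)²/0.25 + 0.1031²/0.05 = 0.173 + 0.239 + 0.213 = 0.625.
- The same split collapsed to 70/30: 0.3477² / (0.70 × 0.30) = 0.576.
- Collapsed to 95/5: 0.1031² / (0.95 × 0.05) = 0.224.
- One cut at a third: 0.595. One cut at the median: 0.637.

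Three ordered groups lose 21% to 38% here, and two groups 36% to 78%.

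Taken together, the loss is about 10% to 40% for three levels. For each distribution where both were computed, collapsing to two loses more.

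**The case against.** Much of the case on the other side stands.

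- A reader might infer that neither named model can suit a three-level outcome. That goes too far. Proportional-odds and multinomial models are logistic regressions, and the text does not restrict the word to binary models.
- A reader might also infer that the percentage delivered is thrown away. The article does not say so. Linear regression may be meant for the proportion and logistic regression for the categories, in which case the linear model loses nothing.
- It is not the only analysis bearing on determinants of implementation. The same section plans regressions of outcomes on implementation strategies, and focus groups will ask about barriers and enablers.
- The figures rest on assumed distributions. The largest losses come from setting a very small extreme group against the rest, a split that the article does not propose.
- The article is condensed and says that it gives the method in brief. Model details for a secondary association analysis often sit in the full plan, and keeping the categories allows comparison with the earlier evaluation.

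What does not fall away is the mismatch in what is stated. The article gives the outcome, its exact cut points and the model families, and they do not join up. If the proportion is the intended outcome of the linear model, the article calls it by a term that it defines only as a category. This is therefore more than a request for detail: a better outcome, already computed, can be named in one sentence.

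**Conclusion.** The point holds as a minor one. As written, the outcome is a coarsened ordered category with no model form matched to it, and the text leaves open whether the underlying proportion is modelled. If the category is what is modelled, the loss is about 10% to 40% of the information with three levels, and more with two. These ranges are illustrations under assumed distributions, because the article gives none. If the linear model is in fact meant for the proportion, it has no such loss and only the wording needs correcting. The claims that both models are unsuitable, or that the percentage is certainly discarded, are not supported. The point concerns the implementation trial's association analyses and does not touch the effectiveness trial's primary outcomes.

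**What to change.** State in the implementation trial's Data analysis section that the modelled outcome is the proportion of the intervention delivered, analysed by linear or fractional-logit regression. Because teachers are nested in schools, add a school random intercept or school-clustered standard errors. Keep low, moderate and high for description and for comparison with the earlier evaluation.

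If the category itself must be modelled, name ordinal logistic regression and report a check of proportional odds. That removes the equal-step assumption and the unstated merger of levels, but not the loss from grouping.

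The change needs a sentence or two and no new data, since the proportion has to be calculated in any case. The cost is slightly less direct comparability of the regression results with the earlier evaluation, which the descriptive categories largely offset.

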### Effectiveness trial

The effectiveness trial will employ a pragmatic waitlist control design. Secondary schools will be assigned (based on the school availability and timing requirements) to the *TransformUs Secondary* intervention (n=5 schools) or a waitlist control ‘usual practice’ condition (n=5 schools). Waitlist control schools will receive the intervention after 6 months (approximately 2–3 school terms).

Following school consent, *TransformUs Secondary* information will be sent to school staff (school leaders and Year 7–10 teachers) via the school’s regular channels of communication (eg, intranet, email or other methods requested by the school). Once organisational and teacher consent is received, plain language statement and consent form documentation will be sent to students (ie, students attending lessons delivered by consenting teachers) and parents (via the school’s regular channels of communication) (online supplemental file 5). There will be two tiers of consent for students. Parents (on behalf of their child) and adolescents will be invited to consent to the following assessments: accelerometer, surveys and classroom observations. In addition, one optional assessment (posture device) will be an opt-in that adolescents can choose to take part in.

### Blinding

Due to the inability to blind schools and teachers to the programme strategies, the study will be conducted as an open trial. Blinding cannot be assured as participation may be disclosed by school staff or students or evident in the school setting (eg, *TransformUs* signage, active environments). The statistician undertaking data analysis will be blinded to the study group, with unlabelled numeric treatment codes being provided.

### Sample size and power calculations

Students will be recruited from 4-year-levels (Years 7, 8, 9 and 10) from each of the 10 schools. It is estimated an average of 15 students will be recruited per year level, enabling at least 12 for analysis, assuming up to 20% dropout. We will conservatively apply a design effect based on an intraclass correlation coefficient (ICC) of 0.03. Assuming an SD for the MVPA outcome of 17 min/day (Corder *et al* 2020), we will have 80% power to detect a minimum difference between groups of 7 min/day MVPA, for α=0.05. Therefore, participants in the effectiveness trial will include one nominated school leader per school (n=up to 10); approximately eight Year 7–10 teachers per school (n=up to 80) and all Year 7–10 secondary students attending classes with the consenting teachers (only consenting student will take part in the evaluation). The recruitment target will be approximately 600 students in total (approximately n=60 students per school). Sample size calculations were conducted in Stata/SE 16 using the power two means command.

Including an effectiveness trial that is accessible to all schools in Victoria enhances the generalisability of the results by incorporating diverse student populations representing various educational contexts, needs and resources. This broad approach improves the reliability of findings, reflecting how the intervention performs across different demographics and settings, making the results more applicable to other schools in the state. However, using a subsample may limit generalisation as it may not fully represent the student population’s diversity. Smaller or more localised samples could be influenced by specific local conditions, reducing the ability to make broader conclusions. While subsamples offer valuable insights, they may lack the comprehensiveness needed for strong generalisations, which we have acknowledged as a limitation.

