### Data analysis

Analysis of the primary and secondary outcomes will be performed using Stata 18 for Windows (StataCorp LP) and RStudio V.1.4.453 (R V.3.6.3; R Foundation for Statistical Computing, Vienna, Austria).

Descriptive analyses will be employed to depict the quantitative data collected for all variables of interest, including students’ demographic characteristics, physical activity, sedentary behaviour, sleep, well-being, class engagement, school environment and intervention implementation measures (eg, school audit data) at each time point. Data will be examined for missing values, outliers and distributional assumptions. Teachers’ demographic characteristics and survey responses from both intervention and control groups will be described.

For the primary outcomes, random intercept linear mixed models will be used (where the unit of the analysis (students) will be nested within year levels within schools) to examine the intervention effects on primary (physical activity and sedentary time) and secondary (sleep and well-being, class and school engagement, reducing sitting time, increasing light, moderate and vigorous physical activity, self-report physical activity/sedentary behaviours, observed physical activity during recess and lunch time and engagement with the intervention strategies) outcomes among adolescents. All models will be adjusted for measured confounders age, gender, baseline values, socioeducational advantage strata (high vs low ICSEA) and school type (Government, Independent, Catholic).

The programme’s reach, adoption, implementation, and organisational-level maintenance aspects will be presented descriptively. Linear or logistic regression models will be used to compare differences between intervention and control groups in teacher perceptions of school readiness, climate, and environment, as well as teacher practices, competence levels, and implementation barriers, adjusting for baseline values as covariates. The school grounds audit data will be analysed using descriptive statistics to characterise the physical environment of intervention and control schools and interactions with the intervention effects will be examined to determine if there was a potential moderator effect by school environment.

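### The stated 80% power for 7 min/day of MVPA relies on a large-sample reference; with 5 against 5 schools the same inputs give about 72%, before any credit for baseline adjustment

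*Protocol article*

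**What the plan says.** The section on the effectiveness trial describes allocation of whole schools: "Secondary schools will be assigned (based on the school availability and timing requirements", with 5 schools in each condition.

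The section on sample size and power calculations gives the numbers. "Students will be recruited from 4-year-levels (Years 7, 8, 9 and 10) from each of the 10 schools", and the expected yield is "an average of 15 students will be recruited per year level, enabling at least 12 for analysis, assuming up to 20% dropout". The total follows: "The recruitment target will be approximately 600 students in total (approximately n=60 students per school". With an ICC of 0.03, an SD of 17 min/day and alpha 0.05, the conclusion is that "we will have 80% power to detect a minimum difference between groups of 7 min/day MVPA". The calculation was done with Stata's two-means power command. The section mentions a design effect, which it calls conservative. It mentions no allowance for the number of schools and no correlation between baseline and follow-up.

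The data analysis section plans random-intercept linear mixed models with students within year levels within schools, and states: "All models will be adjusted for measured confounders age, gender, baseline values, socioeducational advantage strata (high vs low ICSEA) and school type". School type has three categories.

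**The concern.** A design effect corrects the variance of the difference for clustering. It does not account for the between-school variance having to be estimated from very few schools. When schools are allocated, the error term for the intervention effect comes from variation between schools, so its degrees of freedom follow the number of schools and not the number of students. With 5 schools per arm the difference between a normal and a t reference is material.

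This is the only power statement for the effectiveness trial, and it concerns a primary outcome. If it is optimistic, the chance of missing a true 7 min/day effect is greater than the 20% that readers will assume, and a null result could be read as stronger evidence against the programme than it is.

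**Working it through.** **Inputs, all from the effectiveness trial sections.** 5 schools per arm; 12 analysed students × 4 year levels = 48 per school; 48 × 5 = 240 per arm; ICC 0.03; SD 17 min/day; difference 7 min/day; alpha 0.05. Two assumptions are needed. The test is taken as two-sided, because sidedness is not stated. The ICC is taken at school level, because its level is not stated and this is the reading that fits the printed figure (a year-level ICC with 12 per cluster would give 97.5% power).

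**Step 1: reproduce the protocol's figure.**
- Design effect = 1 + (48 − 1) × 0.03 = 2.41
- Effective n per arm = 240 / 2.41 = 99.6
- SE of the difference = 17 × √(2 × 2.41 / 240) = 2.409 min/day
- Standardised difference = 7 / 2.409 = 2.906
- Normal power = Φ(2.906 − 1.960) = 82.8%
- Difference detectable with 80% power = (1.960 + 0.842) × 2.409 = 6.75 min/day, which rounds to the stated 7

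A t reference that counts the deflated students as independent gives almost the same power, 82.4%. So the printed claim is a design effect plus a large-sample or student-level reference.

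**Step 2: same SE, school-level degrees of freedom.** The SE and noncentrality parameter (2.906) are unchanged; only the reference distribution changes, to a noncentral t. With 10 schools and two arms, df = 10 − 2 = 8. If the ICSEA stratum (1 df) and school type (2 df) are also charged, df = 8 − 3 = 5.

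| Reference | Power at 7 min/day | Difference detectable with 80% power |
|---|---|---|
| Normal | 82.8% | 6.75 |
| t, 8 df | 72.1% | 7.71 |
| t, 5 df | 64.5% | 8.47 |

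The 5-df row assumes that the school-level covariates are balanced between arms and explain no between-school variance. Imbalance would lower it; explained variance would raise it.

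**Step 3: sensitivity of the 8-df figure to the other inputs.**
- No dropout (60 analysed per school, design effect 2.77): 75.6%
- ICC 0.02: 80.9%; ICC 0.04: 64.5%
- Unequal school sizes, with an assumed coefficient of variation of 0.4: 68.2%

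**Step 4: what baseline adjustment could return.** Assume that adjustment multiplies both between- and within-school variance by (1 − r²), where r is the baseline to follow-up correlation. The protocol gives no r, so a range is shown.

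| r | Power, 8 df | Power, 5 df |
|---|---|---|
| 0 | 72.1% | 64.5% |
| 0.3 | 76.0% | 68.5% |
| 0.4 | 79.3% | 71.8% |
| 0.5 | 83.5% | 76.4% |
| 0.6 | 88.7% | 82.4% |

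Power of 80% is reached at r of about 0.42 with 8 df, and about 0.56 with 5 df.

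**The case against.** The strongest reply is that the planned analysis adjusts for baseline values, so the unadjusted figure understates the power of the test that will be run. That stands as far as it goes: at a moderate correlation the planned model would reach 80%. It does not rescue the printed statement, which neither states nor uses a correlation.

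A second reply is that the arithmetic reproduces and the inputs are cautious: analysed numbers are given as a minimum, dropout as a maximum, and the ICC allowance is called conservative. The arithmetic does reproduce; the fault lies in the reference distribution. Retaining every recruited student still leaves 75.6% with 8 df. A true ICC of 0.02 would bring it to 80.9%, but the stated claim is for 0.03.

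Three stronger readings are tempting, and the document does not support them:

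- **That the planned model has 65% power.** That figure charges 3 degrees of freedom for ICSEA and school type but credits no variance reduction from the baseline values in the same model. It is a conditional lower scenario.
- **That the primary test has an inflated type I error.** This would follow if z-tests, or maximum likelihood with z-tests, were used. The article specifies neither, and the estimation and degrees-of-freedom method may properly be left to the statistical analysis plan.
- **That ICSEA and school type should be collapsed to save degrees of freedom.** Allocation is by availability and timing, not at random, and the protocol treats these variables as confounders. Collapsing them gives up confounding control, which is a trade-off and not a correction.

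**Conclusion.** The point holds for the power statement as printed. On the protocol's own inputs, and with the 8 school-level degrees of freedom that a 5 against 5 comparison has at most, power for 7 min/day is about 72%, not 80%. The difference detectable with 80% power is about 7.7 min/day. The chance of missing a 7 min/day effect is then about 28%, not 20%, before baseline adjustment.

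This rests on a two-sided test, a school-level ICC of 0.03, an SD of 17 min/day and equal school sizes. Under the further assumptions given for 5 df, the figures are about 65% and 8.5 min/day.

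A reader might infer that the trial is underpowered for its target. The document does not settle that. Whether the planned adjusted analysis reaches 80% depends on a correlation that the protocol does not give: about 0.42 or more with 8 df, or 0.56 or more with 5 df, if adjustment shrinks both variance components equally.

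**What to change.** Change the power statement in one of two ways:

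1. State that, before baseline adjustment and with 8 school-level degrees of freedom, the design has about 72% power for 7 min/day, or 80% power for about 7.7 min/day. The 5-df scenario (about 65%, or 8.5 min/day) can be added with its assumptions.
2. State the baseline to follow-up correlation relied on, with its source, and recompute with a t distribution on school-level degrees of freedom.

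As a matching recommendation, fit the primary mixed model by REML with Kenward-Roger or Satterthwaite degrees of freedom, here or in the statistical analysis plan, so that the test agrees with the restated power. Keep ICSEA and school type in the model as planned.

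The cost is small: a less favourable printed figure under the first option, or a justified correlation under the second, plus options in the model command. Neither needs more schools or students.
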